**Exclusion criteria**

1. < 18 or > 85 years old.
2. Pregnancy and lactation.
3. Serious heart, liver, kidney and hematopoietic system diseases, abnormal liver or kidney function.
4. Suffering from other known virus pneumonia.
5. Allergic to Chinese herbal medicine or suffering from allergies.
6. Critical patients ( respiratory failure treated by mechanical ventilation or shock or multiple organ failure).

**Criteria for discontinuing**

1. The participant decides to discontinue the intervention, the trial or data collection at any time for any reason.
2. Non-compliant patient.
3. In the case of the onset of serious adverse events.
4. The aggravating pathology changes which require ventilator support for treatment during the intervention.

Participants discontinued the trial will be recorded throughout the intervention and followup periods, their data will be collected in the case report form. If the trial wouldn’t continue due to serious adverse events or aggravated illness, appropriate treatment will be taken.

**Sample size**

Based on previous clinical practice of using TCM fought against SARS and H1N1 influenza patients [23], it is estimated the median survival time in the TCM group as 3 days, and 1.5 times longer in the control group. Concerning the analysis of the primary endpoint, the duration of time before improvement of at least one of the common cold-like symptoms (fever, cough, malaise, shortness of breath) , will be estimated using the Kaplan-Meier method, and

the survival curves will be compared between groups using the log-rank test. And this study is designed to detect a statistically significant difference with a level of 5% and a power of 70% (one-sided type-1 error of
[figure not shown]
 =5%，
[figure not shown]
 =30%), so approximately 61 participants in each group will be needed. Thus, under the prediction of a dropout rate of 10%, the sample size of 140 participants will be sufficient to detect a clinically important difference in this trial.

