**Inclusion criteria**

1. Participants are 18-85 years of age, either male or female.
2. Diagnosed as positive for severe acute respiratory syndrome coronavirus 2 (SARS-CoV-2)
3. Symptomatic. Mild (mild clinical symptoms without signs of pneumonia in chest X-ray), and Moderate (fever or [respiratory](../../../../C:/Users/[name]/Downloads/%25E6%259C%2589%25E9%2581%2593/Dict/8.9.0.0/resultui/html/index.html" \l "/javascript:;) [symptom](../../../../C:/Users/[name]/Downloads/%25E6%259C%2589%25E9%2581%2593/Dict/8.9.0.0/resultui/html/index.html" \l "/javascript:;) with signs of pneumonia in chest X-ray) .
4. Signed the informed consent before treatment.
5. Agreed not to enroll in any other clinical trials.
6. Inpatients

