**MEASUREMENTS**

***Primary Outcome***

The primary outcome will be the number of days until the clinical symptom of fever improves in the first 14 days of treatment following randomisation. Fever will be defined as an improvement when the temperature is less than 37℃.

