**Rate of symptom recovery**

The rate of symptom (fever, cough, malaise, shortness of breath) recovery will be one of the secondary endpoints. Fever denoted the subaxillary temperature being 37 degrees or greater. The cough and malaise was self-reported by the patients. Recovery of symptoms will be defined as the complete resolution of fever, cough, malaise, shortness of breath.

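### The protocol names conflicting primary outcomes, and if time to temperature below 37 degrees governs, the stated 70% power is unsupported because fever is not required for entry

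*Protocol*

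**What the plan says.** The protocol describes its primary outcome in three ways.

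- **Abstract and Sample size:** days until at least one of fever, cough, malaise or shortness of breath improves.
- **Primary Outcome (under Measurements):** days until fever improves within 14 days of randomisation. The event rule is "Fever will be defined as an improvement when the temperature is less than" 37℃.
- **Coronavirus nucleic acid test:** time to two consecutive negative RT-PCR results. It stands under Secondary outcomes but is called the primary outcome in the text.

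The Sample size section takes these inputs: "it is estimated the median survival time in the TCM group as 3 days, and 1.5 times longer in the control group"; "the survival curves will be compared between groups using the log-rank test"; and a "power of 70% (one-sided type-1 error of" 5%. It arrives at about 61 per group, allows 10% for dropout, and concludes that "the sample size of 140 participants will be sufficient to detect a clinically important difference in this trial".

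The Inclusion criteria do not require fever. Mild disease means "mild clinical symptoms without signs of pneumonia in chest X-ray". Moderate disease means fever or a respiratory symptom, with pneumonia on imaging. The Exclusion criteria set no temperature limit. Under Rate of symptom recovery, "Fever denoted the subaxillary temperature being 37 degrees or greater".

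**The concern.** By the protocol's own definitions, having no fever and having reached the fever endpoint are the same state: below 37 degrees. A patient admitted with cough alone therefore satisfies the Primary Outcome rule before any treatment. The protocol does not say how such patients are handled, and the sample size allows only for dropout.

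If they are kept as events at time 0, they add identical events to both arms, pull both Kaplan-Meier curves down at the start and dilute the comparison. If they are set aside, fewer patients carry information than the calculation assumed. The choice between these handlings, and between the three endpoints, also stays open in a trial whose patients and treating clinicians know the allocation.

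**Working it through.** **Inputs.** From Sample size: medians of 3 days (TCM) and 3 × 1.5 = 4.5 days (control), one-sided 5%, power 70%, log-rank test, 10% dropout, 140 randomised. From Primary Outcome: 14 days of observation. Assumed here: exponential times, so the hazard ratio is 4.5/3 = 1.5, and, for the fever endpoint, the same medians. The febrile share is not in the documents, so it is varied.

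**Step 1. Reproduce the plan's figure, with every patient at risk.**

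- Events needed (Schoenfeld): 4 × (1.645 + 0.524)² / (ln 1.5)² = 114.5, rounded up to 115.
- Probability of an event by day 14: TCM 1 − 2^(−14/3) = 0.961; control 1 − 2^(−14/4.5) = 0.884; mean 0.922.
- Patients: 115 / 0.922 = 124.7, or 62.3 per group, which is 63 rounded up. The plan says about 61.
- Dropout: 63 / 0.9 = 70 per group, or 140 in total.

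So the plan's figure reproduces approximately for an endpoint that every participant can still reach after baseline.

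**Step 2. Margin in the design.** After 10% dropout, 140 × 0.9 = 126 are evaluable and 126 × 0.922 = 116.2 events are expected. Power = Φ(√116.2 / 2 × 0.4055 − 1.645) = Φ(0.541) = 70.6%. There is almost no slack.

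**Step 3. Fever endpoint with febrile share f.** With afebrile patients set aside, power = Φ(√(116.2 f) / 2 × 0.4055 − 1.645). With afebrile patients kept as day-0 events, power comes from simulated one-sided log-rank tests with 63 per group. These were run with daily readings and with readings only on days 3, 7, 10 and 14, the days listed in the Abstract and Fig. 2. Repeated simulation runs agree within about 3 points.

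| Febrile share | Febrile evaluable | Expected events among them | Power, set aside | Power, day-0 events, daily | Power, day-0 events, days 3/7/10/14 |
|---|---|---|---|---|---|
| 100% | 126 | 116.2 | 70.6% | about 70% | about 68% |
| 90% | 113.4 | 104.6 | 67% | about 62% | about 59% |
| 80% | 100.8 | 93.0 | 62% | about 52% | about 49% |
| 70% | 88.2 | 81.4 | 57% | about 44% | about 40% |
| 60% | 75.6 | 69.7 | 52% | about 39% | about 33% |
| 50% | 63.0 | 58.1 | 46% | about 32% | about 27% |

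**Step 4. Break-even for 70% with afebrile patients set aside.** With the planned dropout, f = 114.5 / 116.2 = 0.985. With no dropout, 140 × 0.922 = 129.1 events are expected if all are febrile, so f = 114.5 / 129.1 = 0.887, about 89%.

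**The case against.** The strongest reply is that the Sample size section is not wrong on its own terms. It names the four-symptom endpoint, under which a patient with cough alone is at risk and informative, and its arithmetic holds. This stands. A reader might infer from the fever definition that the sample-size calculation is in error, or that 140 patients cannot deliver 70% power. The documents do not support either. The shortfall arises only if the Primary Outcome section governs.

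Three further points also stand.

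- The 3 and 4.5 day medians belong to the four-symptom endpoint. Every power figure for fever borrows them, and the table varies the febrile share but not the fever-specific effect.
- The fever threshold is low, so the febrile share could be high. Above about 98.5%, or about 89% with no dropout and afebrile patients set aside, 70% power is kept.
- Counting afebrile patients as day-0 events is only one reading. A patient without fever has no fever to improve, which points to the milder set-aside figures.

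It may also be said that an analysis plan, not shown here, could settle the analysis set. But eligibility, the primary outcome and the sample size are all fixed in the protocol, and these sections do not fit one another. Nor is the four-symptom endpoint free of the problem. The only improvement threshold given for any of the four symptoms is temperature below 37 degrees, so on a literal reading an afebrile patient has already met one component.

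**Conclusion.** The concern holds in conditional form. The protocol contradicts itself on the primary outcome, and the power statement was derived for only one of the versions. If fever resolution governs, the stated 70% is unsupported for two reasons: afebrile patients are eligible and meet the event rule at randomisation, and no medians are given for fever.

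On borrowed medians and 126 evaluable patients, the loss is about 4 points at 90% febrile (67%) and about 25 points at 50% febrile (46%) when afebrile patients are set aside. It is larger when they count as day-0 events. How large it is in this trial cannot be said from the documents. If the four-symptom endpoint governs and improvement is counted only in symptoms present at baseline, the sample size stands approximately as written.

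**What to change.** 1. Before analysis, reconcile the Abstract, Sample size, Primary Outcome and Coronavirus nucleic acid test sections to one primary endpoint.
2. If it is fever resolution, define the primary analysis set as all randomised participants with an axillary temperature of 37 degrees or more at D0, using the protocol's own fever definition. Specify the D0 reading taken before allocation, since Fig. 2 places screening and randomisation on the same day; the comparison then stays randomised. Analyse the other participants for the secondary outcomes. Replace the power sentence by power as a function of the febrile share, filled in from the febrile count pooled over both arms, and state that the medians are assumed for fever.
3. If the four-symptom endpoint is kept, count improvement only in symptoms present at D0, so that absence of fever at baseline is not an event.

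The cost is amendment wording and, under option 2, a less favourable power statement. No extra patients are needed. The set in option 2 avoids uninformative day-0 events but does not restore 70% power. It should not be applied if the four-symptom endpoint is chosen, because it would then drop informative patients.

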**Randomization**

Minimization method will be used, with balancing of the arms with pneumonia severity. Patients are randomized (1:1 ratio) to each group. Clinical researchers will get a random sequence number which is automatically generated by a random number generator (IBM Corp., Armonk, NY, USA), and sequentially number them in an opaque envelope. Researchers will open random allocation envelopes and assign participants accordingly. Eligible patients will be randomly divided into a routine supportive care group and a routine supportive care plus oral administration of traditional Chinese medicine group, with 70 patients in each group.

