**STATISTICAL ANALYSIS**

We will use log-rank test for the primary outcome, if the influence of confounding factors needs to be considered, Cox proportional hazard model can be used. For all secondary outcomes, Wilcoxon rank sum test will be used. For safety evaluation of TCM, two-sided t-test will be applied to each safety measurement after data normalization.

To better understand the nature the missing mechanisms, we will characterize the type of subjects who have missing data, then statistical models to impute missing values if the assumption of missing at random is met will be used.

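### The Randomization section names minimisation on severity but describes a fixed envelope sequence, and, as a separate matter, the primary log-rank test does not commit to using severity

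*Protocol*

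**What the plan says.** **Allocation (Protocol, Randomization).** The section opens with "Minimization method will be used, with balancing of the arms with pneumonia severity" and adds "Patients are randomized (1:1 ratio) to each group". It then sets out the mechanics: "Clinical researchers will get a random sequence number which is automatically generated by a random number generator", the researchers "sequentially number them in an opaque envelope", and "Researchers will open random allocation envelopes and assign participants accordingly". It ends by fixing the arm sizes, "with 70 patients in each group". It describes no tally of earlier patients by severity and arm, no separate envelope sets for Mild and Moderate patients, and no central or computer-run step.

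**Analysis (Protocol, Sample size and STATISTICAL ANALYSIS).** Both sections name a log-rank test for the primary outcome, and neither mentions stratification. The analysis section then adds "if the influence of confounding factors needs to be considered, Cox proportional hazard model can be used". It names no covariate and gives no rule for when the clause applies.

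The Inclusion criteria define two severity levels, Mild and Moderate, separated by signs of pneumonia on chest X-ray. The Protocol gives neither the expected share of each nor the effect of severity on time to improvement.

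**The concern.** There are two points, and they do not depend on each other.

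First, the allocation text describes two different procedures. Minimisation derives each new allocation from the severity and arm of the patients already enrolled. A single sequence fixed in advance takes no account of the next patient's severity. A reader cannot tell which procedure was followed. If the envelopes held one simple sequence, the severity balance that the section promises was left to chance.

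Second, severity is the only factor that the trial sets out to balance, yet the primary test does not use it. If severity predicts time to improvement, an unstratified test gives up power. If the balancing worked, that test is also conservative. The design power is only 70% with a one-sided 5% error, so there is little to spare. The conditional clause on the Cox model leaves open which result is the adjusted one and when it would be produced.

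**Working it through.** **1. The plan's own sample size.** Inputs from the Sample size section: medians of 3 days and 1.5 × 3 = 4.5 days, one-sided 5%, power 70%, 61 per group. The Primary Outcome section gives 14 days of observation.

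- Exponential times give a treatment hazard ratio of 4.5/3 = 1.5.
- Schoenfeld events: 4 × (1.645 + 0.524)² / (ln 1.5)² = 114.5, so 115.
- Probability of an event by day 14: 1 − 2^(−14/3) = 0.961 on TCM and 1 − 2^(−14/4.5) = 0.884 on control, mean 0.922.
- Per arm: 115 / (2 × 0.922) = 62.3. The exponential formula without censoring gives 61.2.

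The stated 61 is therefore reproduced to within 2 patients by a one-sided, unstratified log-rank calculation. No term for severity enters it.

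**2. Balance if the envelopes hold one simple sequence.** Take 70 per arm and treat the number of Moderate patients in each arm as binomial. A gap of 10 points is 7 patients out of 70. The severity mix is assumed.

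| Share Moderate (assumed) | Gap of 10 points or more | Gap of more than 10 points |
|---|---|---|
| 50% | 27% | 20% |
| 30% or 70% | 23% | 17% |
| 20% or 80% | 17% | 11% |

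**3. Power with and without severity in the test.** Simulation with 61 per arm, exponential times, control median 4.5 days at average severity, treatment hazard ratio 1.5 within each severity level, censoring at day 14, one-sided 5%, 50% Moderate (assumed). There were 6,000 runs per setting, with a Monte Carlo standard error of about 0.6 points.

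| Severity HR (assumed) | Arms balanced: unstratified v stratified | Arms not balanced: unstratified v stratified |
|---|---|---|
| 1 | 69.2% v 69.0% | 69.9% v 68.3% |
| 1.5 | 67.4% v 68.6% | 66.5% v 68.1% |
| 2 | 61.9% v 67.4% | 62.2% v 67.3% |
| 3 | 53.9% v 66.5% | 53.3% v 66.6% |

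- Across columns, unstratified test: balancing changes its power by 1 point or less at every severity effect.
- Within the balanced column: stratifying gains about 0, 1, 6 and 13 points.
- At severity HR 2 with balanced arms, 20% Moderate gives 65.0% v 68.9% and 80% Moderate gives 65.8% v 68.4%, a gain of about 3 to 4 points.

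**4. Type I error, same settings with treatment HR 1.**

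- Unstratified, arms not balanced: 5.0% to 5.4%.
- Unstratified, arms balanced: 5.1%, 5.0%, 4.5% and 3.4% at severity HR 1, 1.5, 2 and 3.
- Stratified: 5.1% to 5.6% throughout.

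**The case against.** Several stronger readings are tempting, and the documents do not support them.

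- *Minimisation cannot be run from envelopes, so the trial used simple randomisation.* With one two-level factor, minimisation amounts to balanced allocation within each level, and separate envelope sets for Mild and Moderate patients could deliver that. The section does not say that there is only one list. It also fixes 70 per group, which unrestricted simple randomisation does not guarantee. The text is contradictory; it does not establish what was done.
- *Failed balance costs power or invalidates the test.* The simulation shows neither. Without balancing, power moves by 1 point or less and type I error stays near 5%. A chance imbalance can still distort one particular result.
- *Power is lost.* This is conditional. Nothing in the documents shows how strongly chest X-ray signs predict time to a temperature below 37℃. At a severity hazard ratio of 1.5 the loss is only 1 to 2 points.
- *There will be two primary p-values.* The analysis section names the log-rank test as primary and says only that a Cox model may be used. The Blinding section keeps data analysts blinded throughout, which limits choosing by result. It does not supply the missing rule, however.
- *Hospital should also be balanced.* The Protocol never promises this, and nothing in it shows a hospital effect.

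A fair further objection is that stratification and covariates are often fixed in a statistical analysis plan, which is not shown here and may settle the matter. That stands as a limit on the second point. What remains is that the Protocol itself names the primary test and attaches an open-ended alternative to it.

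**Conclusion.** Both points hold, separately. The Randomization section contradicts itself on the allocation method, and this needs no assumption. Its possible consequence, a gap of 10 points or more in the Moderate share in about 27% of trials, applies only if one simple sequence was used with 70 per arm and 50% Moderate. The figure falls with a more uneven mix.

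The primary test does not commit to the one factor that the trial balances on. With 50% Moderate, the cost runs from nothing if severity is not prognostic to about 6 points of power at a severity hazard ratio of 2 and 13 at 3. These figures rest on an assumed mix, assumed severity effects, exponential times and a treatment hazard ratio of 1.5 within each severity level. A reader might quote 54% v 67% as the expected loss, but it is the upper end of an assumed range. The case for stratifying does not need it: the change costs almost nothing and, if balancing did work, it brings a conservative test back to about its nominal level.

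**What to change.** 1. **Randomization section.** Replace the text with the method actually used since recruitment began in March 2020: minimisation with its procedure (tally, any random element, who ran it), envelope lists specific to each severity level, or simple randomisation. If it was simple randomisation, withdraw the statement that severity is balanced. No new allocation system is asked for. Version 2.0 is dated 14 October 2020 and recruitment is due to end on 31 December 2020, so a change at three hospitals would not be cheap.
2. **STATISTICAL ANALYSIS section, with the matching sentence under Sample size.** Make the primary test a log-rank stratified by severity (Mild, Moderate), report the hazard ratio from a Cox model with arm and severity, and delete the conditional clause. Date the change before anyone sees unblinded data.

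The cost is a correction of wording. If severity turns out not to be prognostic, the simulated loss from stratifying is 0.1 points with balanced arms (69.2% v 69.0%, before rounding 69.15% v 69.02%) and 1.6 points without balancing (69.9% v 68.3%). Given the simulation error, that is about one point.

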**Participants and Recruitment**

Participants will be recruited from 3 hospitals, the First Affiliated Hospital of Wenzhou Medical University, the Second Affiliated Hospital of Wenzhou Medical University and Wenzhou Center Hospital. These 3 hospitals are appointed to treat patients with COVID-19. To recruit target subjects, the study researchers will send a message to every inpatient when they are diagnosed with SARS-CoV-2. If the inpatients are eligible and interested in taking part in the study, they will be fully informed of the project information including the study procedures, potential benefits and risks. Written informed consent includes provisions for use of study data and biological specimens in future researches will be obtained from the patient or their substitute decision-makers before the allocation. All participant have the right to withdraw from the study at any time.

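### The protocol does not separate the staff who hold the random sequence and prepare the envelopes from the staff who recruit and assign patients, so the next allocation could be known before a patient is entered.

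*Protocol*

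**What the plan says.** The Protocol, Randomization, describes the procedure in a few sentences:

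- Method: "Minimization method will be used, with balancing of the arms with pneumonia severity", at a 1:1 ratio, "with 70 patients in each group".
- Source of the sequence: "Clinical researchers will get a random sequence number which is automatically generated by a random number generator".
- Preparation: the same clinical researchers then "sequentially number them in an opaque envelope".
- Use: "Researchers will open random allocation envelopes and assign participants accordingly".

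Participants and Recruitment says that study researchers contact every inpatient diagnosed with the virus at three hospitals. Blinding says that patients and treating clinicians know the allocation, while outcome assessors and data analysts do not.

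Consent timing appears in two places. Participants and Recruitment says that written consent "will be obtained from the patient or their substitute decision-makers before the allocation". Inclusion criterion 4 reads "Signed the informed consent before treatment". The schedule in Fig. 2 lists eligibility screen, informed consent and randomization in that order, all on D0, with treatment from D1.

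**The concern.** Concealment requires that the person deciding whether to enter a patient cannot know the next assignment. The Randomization section names no statistician, pharmacy or central service as holder of the sequence. It gives the list and the envelopes to clinical researchers, and gives the opening to researchers without further description. An opaque, numbered envelope hides its content only from people who did not fill it.

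Blinding cannot cover this gap. Blinded assessors and analysts act after entry, and patients and clinicians are not blinded at all. If patients expected to recover quickly were entered more readily when the next envelope held the herbal arm, the arms would differ before treatment. The log-rank test would read that difference as effect. The Cox model in Statistical Analysis is optional, names no covariates, and cannot adjust for features that were not recorded.

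**Working it through.** **1. Who does what.**

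| Step | Who, according to the Protocol | Separation stated? |
|---|---|---|
| Approach patients | study researchers | no |
| Obtain sequence, number envelopes | clinical researchers | no |
| Open envelopes, assign | researchers | no |
| Assess outcomes, analyse | blinded assessors and analysts | yes, by blinding, but only after entry |

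No sentence bars the holder of the list from screening or enrolling. The stated safeguards are opacity and sequential numbering. Sealing is not mentioned, nor is a rule on when an envelope may be opened.

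**2. Consent timing.** Consent before allocation is also consent before treatment, so the recruitment section and criterion 4 can both be met, and the stricter one governs. The order in Fig. 2 agrees with it. The eligibility checklist taken alone would not catch a consent signed between randomization on D0 and treatment on D1, but such a consent would breach the recruitment section.

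**3. The plan's own figure.** The document gives no number for concealment. The illustration below uses the planned 61 per group, so that was reproduced first. Inputs from Sample size: medians 3 and 4.5 days (hazard ratio 1.5), one-sided 5%, power 70%. (1.645 + 0.524)² = 4.706.

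- Freedman: 4.706 × (2.5/0.5)² = 117.6, so 118 events, or 59 per group.
- Schoenfeld: 4 × 4.706 / (ln 1.5)² = 114.5, so 115 events. Dividing by the mean 14-day event probability of 0.922 gives 124.7, or 63 per group.
- Dropout: 61/0.9 = 67.8, so 68 per group and 136 in total.

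The stated 61 and 140 are consistent with this. There is no numerical dispute.

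**4. Illustration of size.** The assumptions, none of them from the document, are: no treatment effect; half the patients recover at twice the daily rate of the rest; exponential times; fast recoverers unevenly split by selection at entry; no balancing on that feature. Taken from the plan: 61 per arm, overall median 4.5 days, follow-up to day 14, one-sided 5%.

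Slow rate λ: 0.5e^(−4.5λ) + 0.5e^(−9λ) = 0.5. With x = e^(−4.5λ), x² + x − 1 = 0, so x = 0.618 and λ = 0.107 per day. Event probability by day 14: 1 − (0.224 + 0.050)/2 = 0.863, so about 122 × 0.863 = 105 events.

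Simulated log-rank tests gave:

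| Fast recoverers, herbal vs control | Spurious hazard ratio | One-sided rejection |
|---|---|---|
| 50% vs 50% | 1.00 | about 5% |
| 55% vs 45% | about 1.07 | about 10% |
| 60% vs 40% | about 1.14 | about 17% |

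Hand check, 1 − Φ(1.645 − ln HR × √(105/4)): for 1.07, 1.645 − 0.068 × 5.12 = 1.30, giving 10%. For 1.14, 1.645 − 0.131 × 5.12 = 0.97, giving 17%. In patients, 55/45 is 33.6 against 27.5 of 61, a difference of about 6. For 60/40 it is 36.6 against 24.4, about 12.

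**The case against.** The strongest reply is that the text does not show anyone holding both the list and the recruitment decision. It uses three labels (clinical researchers, researchers, study researchers) and never says they are the same people. A reader might infer that one team does every step and sees the list while recruiting. The document does not support that: it only fails to keep the roles apart. Opaque, sequentially numbered envelopes are also a real, partial safeguard against a recruiter who did not prepare them. Both points stand, and they limit the claim to what the procedure permits.

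A reader might also infer from criterion 4 that consent may follow the opening of the envelope, which would be a second route to foreknowledge. That does not hold. The recruitment section requires consent before allocation and Fig. 2 lists it ahead of randomization, so criterion 4 is only the looser of two compatible wordings.

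Third, pneumonia severity is balanced between arms, so steering milder patients as a class is largely blocked. That stands. Selection within a severity level, for example on age, days since onset or baseline fever, is not blocked.

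Last, the simulated error rates rest on assumed splits and an assumed twofold rate. They show sensitivity to an imbalance. They are not evidence that this trial has one.

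**Conclusion.** The point holds as a weakness of the written procedure. Clinical researchers hold the sequence and prepare the envelopes, researchers open them, no independent holder is named, and no separation from recruitment is stated. In an open-label trial this leaves the preparer able to know the next assignment before deciding whom to enter. Severity balancing narrows the room for selection without closing it.

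It does not follow that foreknowledge was used, that recruiters have seen the list, or that the protocol allows consent after allocation. The size is unknown. The error rates of about 10% and 17% against a nominal 5% are conditional on the assumed 55/45 and 60/40 splits of patients who recover twice as fast.

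The point deserves action because the integrity of the randomised comparison depends on it, no later analysis can restore it, and the remedy is cheap.

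**What to change.** In Randomization:

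1. Reconcile the two descriptions first. Minimization computes each assignment from the patients already entered, whereas a numbered envelope holds an assignment fixed in advance. State which is used.
2. Have the sequence, or the minimization assignments, generated and held by existing staff with no part in recruitment, care, outcome assessment or analysis, and say how this works at all three hospitals. State that recruiting researchers never see it.
3. Release each allocation, by sealed envelope or by call, only after eligibility and signed consent are recorded.

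As an editorial alignment only, change inclusion criterion 4 to require consent before randomisation, to match Participants and Recruitment.

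The cost is the reassignment of a clerical task, a release arrangement that reaches three hospitals, and a few reworded sentences. Recruitment began in March 2020, this version is dated 14 October 2020 and completion is expected by 31 December 2020, so the change protects only later patients. For those already entered, document who held the list and who opened the envelopes, and report any lack of concealment as a limitation.
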